## Abstract

Iron (Fe) deficiency anaemia is a public health concern among adolescent girls worldwide. Food-to-food fortification may be a sustainable and effective solution to Fe deficiency anaemia. However, the effect of food-to-food fortification on Fe deficiency anaemia reduction is understudied particularly in Ghana. This study seeks to investigate the efficacy of baobab pulp-fortified pearl millet beverage powder in improving the Fe and anaemia status of adolescent girls in Ghana. A three-arm cluster randomised controlled trial design, which will involve 258 anaemic adolescent girls (86/arm) selected through multi-stage cluster sampling in Kumbungu District of Ghana, will be used. Participants in arm 1 will receive 350 ml of baobab pulp-fortified pearl millet beverage, containing 13 mgFe (96 % of average RDA), 18·8 mg vitamin C (30·4 % of average RDA) and 222·1 mg citric acid, while participants in arm 2 will receive similar volume of unfortified pearl millet beverage, once a day, five times a week, for six months. Participants in arm 3 will receive the routine weekly Fe (60 mg)-folate (400 μg) supplementation for six months. Serum ferritin, C-reactive protein and haemoglobin (Hb) of participants will be assessed at baseline and end-line. The primary outcomes will be serum ferritin and Hb concentrations. Secondary outcomes will be prevalence of Fe deficiency, Fe deficiency anaemia and BMI-for-age. One-way ANOVA and paired *t* test will be used to compare means of serum ferritin and Hb levels among and within groups, respectively. This study will provide novel concrete evidence on the efficacy of pearl millet-baobab pulp beverage powder in improving Fe and anaemia status of adolescent girls.

Anaemia among adolescent girls is a global public health concern as about half of them are anaemic^(1)^. Likewise, nearly half of adolescent girls in Sub-Saharan Africa are anaemic^(2)^. In Ghana, the prevalence of anaemia among adolescent girls aged 15–19 years and 10–19 years stands at 48 %^(3)^ and 50·1 %^(4),^ respectively, and as high as 64 % among rural adolescent girls (10–19 years)^(5)^. Anaemia has a deleterious impact on growth and development, work and academic performance, physical and mental capacity, and reproductive health of adolescent girls^(6)^.

Fe deficiency is the main cause of anaemia among adolescent girls^(7)^. Adolescence is a period of fast growth with an acute rise in blood volume, lean body mass and red blood cell mass, which results in a surge in Fe requirement for the synthesis of Hb and myoglobin^(8)^. Adolescent girls are more vulnerable to Fe deficiency compared to their male counterparts because of the monthly loss of Fe through menstruation^(9)^. They are three times more likely to be Fe deficient as compared to adolescent boys^(6)^. Other factors such as poor bioavailability of dietary Fe, low dietary intake of Fe, infectious diseases and parasitic infections also contribute to Fe deficiency^(8,10)^. The determinants of anaemia are context-specific^(11)^, and in Ghana, some of the contextual determinants of anaemia include poor nutritional knowledge, intestinal worms, diarrhoea, food, malaria and poor dietary intake^(12)^. The diets of adolescents, particularly rural adolescents in Ghana, are largely plant-based^(13),^ and bioavailability of Fe from such diets is limited^(14)^; hence, most adolescent girls are unable to meet the increased Fe requirements during adolescence caused by high growth spurt and the loss of Fe each month through menstruation.

In Ghana, Fe food fortification and Fe supplementation are the main interventions in place to address Fe deficiency anaemia among adolescent girls^(15)^. However, these approaches have challenges in terms of acceptability, sustainability and affordability in developing countries^(16–19)^. Food-to-food fortification which utilises locally available foods is recommended as a good alternative measure for addressing micronutrient deficiency in developing countries, as it overcomes the aforementioned challenges of the conventional approaches^(16,17)^. Food-to-food fortification is the addition of a locally available and accessible micronutrient dense food to another locally available and accessible food to enhance the bioavailability of micronutrients to populations^(17)^. In Ghana, food-to-food interventions have been shown to improve Fe status of lactating mothers^(20)^ and anaemia status of children aged 6–9 years^(21)^. However, there is scanty data on food-to-food fortification interventions for improving the Fe status of adolescent girls in Ghana.

Cereals are a major staple in Ghana,^(22)^ and pearl millet is the cereal with the highest amount of Fe (15 mg/100 g)^(23)^; however, only about 7·5 % of the Fe is bioavailable for absorption as a result of anti-nutritive factors and the non-heme nature of the Fe^(24)^. Vitamin C and organic acids such as citric acid can enhance non-heme Fe bioavailability and mitigate the inhibitory effect of anti-nutritive factors (polyphenols and phytates) on Fe absorption^(25)^. The explanations for their effect are dual: (1) they prevent the formation of insoluble and unabsorbable Fe complexes and (2) they reduce ferric (Fe^3+^) to ferrous (Fe^2+^) Fe, which is necessary for the absorption of Fe into mucosal cells^(26,27)^. *In vitro* studies^(28,29)^ have revealed that the addition of baobab pulp to pearl millet-based foods greatly enhances Fe bioaccessibility due to its high vitamin C (200 mg/100 g) and citric acid content (3300 mg/100 g), which is exceptional compared to other fruits and vegetables^(30)^. In the *in vitro* study by Adetola et al.^(28)^, baobab fruit pulp was mixed with pearl millet porridge at a ratio of 15:100, which resulted in a significant increase in the proportion of bioaccessible Fe compared with the unfortified pearl millet porridge. Van Der Merwe et al.^(29)^ also found a similar result in their *in vitro* trial when baobab fruit pulp was mixed with pearl millet flour at a 10:100 ratio and recommended based on their finding that baobab pulp-fortified pearl millet beverages could improve Fe status in women and vulnerable groups, but the extent of improvement can only be determined through clinical trials. However, efficacy trials are yet to be done to confirm these findings as per literature. This study therefore seeks to investigate the efficacy of pearl millet instant beverage powder enriched with baobab fruit pulp in improving Fe and anaemia status of anaemic adolescent girls in rural Ghana. We hypothesise that baobab pulp-fortified pearl millet beverage powder will enhance Fe and Hb status, compared to the unfortified pearl millet beverage powder, in adolescent girls in rural Ghana. We also hypothesise that baobab pulp-fortified pearl millet beverage powder will have a similar or greater effect on Fe and Hb status, compared to the routine Fe -folate supplementation, in adolescent girls in rural Ghana.

## Methods

### Study design

The study will be a three-arm parallel cluster randomised controlled trial. Participants in arm 1 (Intervention group) will receive pearl millet beverage enriched with baobab pulp, while participants in arm 2 (Control group 1) will receive unfortified pearl millet beverage, once a day, five times a week, for six months. Participants in arm 3 (Control group 2) will receive weekly Fe -folate supplementation also for six months. The study outcomes will be assessed twice, at baseline and end-line.

### Study area

The study will be carried out in basic schools in Kumbungu District of Northern Ghana. In Ghana, the rural northern savannah agro-ecological zone has the highest prevalence of anaemia among adolescent girls (64·4 %)^(31)^, with the highest prevalence in the Kumbungu District (75 %)^(32)^.

### Study population

The study population will comprise of adolescent girls aged 10–19 years (pre- and post-menarche girls) attending Upper Primary (Primary 4–6) and Junior High Schools in Kumbungu District. The study is to include both pre- and post-menarche adolescent girls because the average Fe requirement is not greatly different between the two groups (0·3 mg difference)^(7)^. However, data analysis will also be stratified by menarche status to explore any possible menarche status-related differences.

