#### Formulation and preparation of beverages

Two powder formulations will be made: (1) baobab pulp-fortified pearl millet beverage powder for the intervention group (arm 1) and (2) unfortified pearl millet beverage powder for the control group 1 (arm 2).

Based on the Ghanaian traditional recipe for the beverage (zomkom), the beverage will be prepared by dissolving the powder mix (60 g millet powder enriched with 9 g baobab fruit powder) in chill/cold water (300 ml) with added sugar (8 g), making a total volume of 350 ml. The amount of baobab powder enrichment was determined based on an acceptability test done among adolescent girls (online Supplementary file 1). The sugar content of the beverage (2·2 g/100 ml) is within the acceptable amount of sugar (≤ 2·5 g/100 ml) in beverages that will have no significant negative impact on BMI and other health outcomes^(47,48)^ and the amount of sugar in the beverage per serving per day (8 g/350 ml) is also far lower than the WHO’s daily recommended maximum amount of free sugar intake for children (50 g, equivalent to 10 % of total energy intake)^(49)^. To test the acceptance of the volume of beverage per serving (350 ml), 40 adolescent girls were fed the beverage over 3 days and all participants comfortably consumed all the 350 ml of the beverage in each feeding session.

The RDA of Fe for adolescent girls aged 10–19 years averages at 13·6 mg (8 mg, 15 mg and 18 mg for girls aged 10–13, 14–18 and 19 years respectively)^(50)^. As in similar studies^(51–53)^, the target of this study is to meet closely the average RDA (13·6 mg) of Fe daily for six months. Hence, the intervention group will receive 350 ml of the baobab pulp-fortified beverage containing 13 mgFe (96 % of average RDA), 18·8 mg of vitamin C (30·4 % of average RDA)^(50)^ and 222·1 mg of citric acid, while the control group 1 will receive similar volume of the unfortified beverage containing 12·4 mgFe (91·2 % of average RDA) once daily, five times a week for six consecutive months. Preparation and formulation of the beverage powders will be done in the Diet Practicum Laboratory at the Department of Nutritional Sciences, University for Development Studies, because of its proximity to the study area.

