### Statistical analysis

Data analysis will be done using Statistical Package for Social Sciences version 22 and WHO AnthroPlus software. Shapiro–Wilk and Kolmogorov–Smirnov tests will be done to test quantitative data for normality. Data that turns out not to be normally distributed will be analysed using non-parametric tests. Continuous data will be reported as means and sd, whilst categorical variables will be presented as frequencies and percentages. Data will be analysed using intention to treat analysis. One-way ANOVA will be used to compare means of serum ferritin and Hb levels among the three study groups (arms). Tukey’s post hoc test of one-way ANOVA will be performed to determine intergroup differences. Paired *t* test will be used to determine change in means of serum ferritin and Hb levels within groups (baseline and end-line). Relationship between covariates and outcome variables will be determined using multivariate linear and binary logistic regression analyses. WHO AnthroPlus software will be used to compute BMI-for-age Z-scores to determine participant’s nutritional status. Missing data will be resolved via multiple imputations. *P* < 0·05 will be considered significant at two-tailed tests.

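### The 0.3 mg reason for including both pre- and post-menarche girls has no stated scale and fits poorly with the protocol's own iron figures; separately, the between-arm ANOVA adjusts for neither age nor menarche status, though both are recorded

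*Protocol article*

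**What the plan says.** Under Study population, the protocol article justifies enrolling both groups "because the average Fe requirement is not greatly different between the two groups", and puts the difference at 0.3 mg. It does not say whether the 0.3 mg is absorbed or dietary iron. It then adds that "data analysis will also be stratified by menarche status to explore any possible menarche status-related differences".

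Two other places bear on the 0.3 mg. Formulation and preparation of beverages gives iron RDAs of "8 mg, 15 mg and 18 mg for girls aged 10–13, 14–18 and 19 years respectively". The introductory text says of pearl millet that "only about 7·5 % of the Fe is bioavailable for absorption".

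On the analysis, Statistical analysis states: "One-way ANOVA will be used to compare means of serum ferritin and Hb levels among the three study groups (arms"), followed by Tukey comparisons. No covariate enters that test. A regression of outcomes on covariates is also planned, but it names no covariates and is not said to yield an adjusted arm effect.

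General characteristics lists age and menarche status among the baseline data. Inclusion criteria sets an upper Hb limit of 11.5 g/dl below 12 years and 12 g/dl from 12 years. Randomisation allocates six schools, two per arm, with a spreadsheet random-number function and no stratification.

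**The concern.** There are two separate matters.

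**Rationale.** A difference of 0.3 mg means one thing on the scale of dietary intake and another on the scale of absorbed iron. The reader cannot tell which is meant, and on neither scale do the protocol's other figures make the difference look small.

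**Analysis.** Iron status plausibly depends on age and menarche status, and the Hb entry ceiling depends on age by design. The mix of girls will vary from school to school, and two schools per arm cannot be relied on to even it out. An unadjusted comparison of arm means then carries whatever age and menarche difference the allocation produced, and part of that could be read as an effect of the beverage or the tablets. The variables needed to reduce this are already being collected.

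**Working it through.** **1. The 0.3 mg against the protocol's other iron figures.** The 0.3 mg comes from a cited source and cannot be reproduced here. It can only be compared. The two readings below are alternatives and must not be combined.

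- *If dietary:* the RDA step from 10–13 to 14–18 years is 15 − 8 = 7 mg, and 7/0.3 = 23 times the stated difference.
- *If absorbed:* at 7.5 % bioavailability, 0.3/0.075 = 4.0 mg dietary (3.0–6.0 mg at an assumed 10–5 %). That is 4.0/8 = 50 % of the youngest group's RDA, 4.0/13.6 = 29 % of the protocol's average RDA and 4.0/13 = 31 % of the iron in one fortified serving.
- *Both on the absorbed scale:* the RDA step becomes 7 × 0.075 = 0.53 mg, and 0.53/0.3 is about 1.75, less than twofold.

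**2. The plan's sample size, as the starting point for power.** With SD 20.1 µg/l, difference 9.4 µg/l and z values 1.96 and 0.84:

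- n = 2 × (20.1 × 2.80/9.4)² = 71.7, so 72 per arm.
- Design effect = 1 + 0.0009 × 42 = 1.0378, and 72 × 1.0378 = 74.7.
- With 15 % added, 74.7 × 1.15 = 85.9, so 86 per arm. The plan's figure is reproduced by this route and does not depend on the present point.

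**3. What imbalance could do to ferritin.** The documents give neither the ferritin gap by menarche status nor the post-menarche share by school, so every input here is an assumption.

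- Shift in the unadjusted difference = (difference in share between two arms) × (ferritin gap). For 20 points and a gap of 4–10 µg/l: 0.20 × 4 = 0.8 to 0.20 × 10 = 2.0 µg/l. Against 9.4 µg/l this is 9–21 %.
- Wider assumptions (10–30 points, gap 5–15 µg/l) give 0.5–4.5 µg/l, or 5–48 %.
- How often: if school shares vary with SD s, the difference between two arms of two schools has variance 2 × s²/2 = s². On a normal approximation, a difference above 20 points between a given pair of arms occurs in 5, 18 or 32 % of allocations for s = 10, 15 or 20 points.
- Cross-check: with a 50 % share, 86 girls per arm and ICC ρ for menarche, the SD of the arm difference is √(2 × 0.25 × (1 + 42ρ)/86). This is 7.6 points at ρ = 0 and 13–17 points at ρ = 0.05–0.10.

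**4. Haemoglobin.** With the plan's SD of 1.2 g/dl and an assumed normal population mean of 10.5–11.5 g/dl in both age groups, the different entry ceilings alone separate mean baseline Hb by about 0.18–0.29 g/dl. A 20-point difference in the share under 12 years would move the baseline arm difference by 0.20 × 0.18 = 0.036 to 0.20 × 0.29 = 0.058 g/dl, or 6–9 % of the planned 0.65 g/dl. It matters at end-line only as far as it persists.

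**5. Precision from adjustment.** The residual SD is 20.1 × √(1 − R²), and power is Φ(9.4/(SD × √(2/72)) − 1.96) with 72 effective girls per arm. This takes the plan's design effect as given and makes no Tukey correction.

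| Assumed R² | Residual SD (µg/l) | Power |
|---|---|---|
| 0 | 20.10 | 80.1 % |
| 0.02 | 19.90 | 80.9 % |
| 0.05 | 19.59 | 82.1 % |
| 0.10 | 19.07 | 84.1 % |

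For scale, a ferritin gap of 5 or 10 µg/l at a 50 % share gives R² = 0.25 × gap²/20.1² = 0.015 or 0.062.

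**The case against.** A reader might infer three stronger things. The documents support none of them.

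- *That the RDAs contradict the 0.3 mg.* The RDAs are set by age band on a dietary scale. The 0.3 mg is by menarche status on an unstated scale, and the cut at 13/14 years is not menarche. On the absorbed scale the figures are within a factor of two. The 7.5 % describes pearl millet, not the girls' whole diet. The sentence that girls are more vulnerable "because of the monthly loss of Fe through menstruation" compares them with boys, not pre- with post-menarche girls.
- *That the 0.3 mg argument led to the unadjusted ANOVA.* The sentence justifies eligibility only. Statistical analysis does not refer to it, and the test would be the same without it. Enrolling and pooling both groups is not itself an error.
- *That menarche status is ignored, or is known to be strongly prognostic.* A stratified analysis and a covariate regression are both planned, and no figure in the documents quantifies prognostic strength.

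Two further objections are fair. Covariate lists are often left to a statistical analysis plan, which is not shown. Also, imbalance between randomised schools is chance variation rather than systematic bias, and all schools recruit from the same grades under age-specific Hb cut-offs, which may narrow the differences.

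What remains is that the article does not merely leave the between-arm test open. It states the test, without covariates. An exploratory split by menarche status does not adjust the overall contrast, and the regression is not described as doing so. Chance imbalance is exactly what baseline adjustment addresses.

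**Conclusion.** The point stands on two unlinked counts. First, the statement that requirements hardly differ is poorly supported by the protocol's own RDAs and bioavailability figure, and its scale is missing. The passages need reconciling; they do not strictly contradict each other. Second, the stated between-arm comparison omits age and menarche status, which are recorded and plausibly prognostic, in a design where two unstratified schools per arm may leave them unbalanced.

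The size is modest and uncertain. The 0.8–2.0 µg/l ferritin shift depends on an assumed gap of 4–10 µg/l and an assumed 20-point imbalance. The power gain, from about 80 % to 81–84 %, depends on an assumed R² of 0.02–0.10. Adjustment would reduce measured imbalance, not abolish it, and it does not replace an analysis that allows for clustering. The planned 86 per arm is unaffected. The change should be made because it is nearly free, not because a large bias has been shown.

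**What to change.** 1. Under Study population, state whether the 0.3 mg is absorbed or dietary iron and reconcile it with the RDAs and the bioavailability figure, or drop it as a reason. Including both groups can stand without it.
2. Under Statistical analysis, replace the unadjusted ANOVA with a prespecified between-arm model for end-line ferritin and end-line Hb over all girls. Baseline menarche status, age and the baseline value of the outcome should be covariates, within an analysis that respects clustering by school.
3. Keep the results by menarche status and label them exploratory.

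The cost is a few sentences and no new data, since every covariate is already collected at baseline. With six schools in three arms, a school-level comparison has only 6 − 3 = 3 degrees of freedom. The covariates should therefore enter at the level of the girl, and the change should not be presented as curing the small number of clusters.

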### Sample size

The formula employed for the sample size estimation is: N = 2S

(

+

/

^(36)^

where N is sample size

sd is standard deviation; estimated to be 20·1 μg/l for serum ferritin^(37)^ and 1·2 g/dl for Hb (anaemia)^(32)^.

 = 1·96 (From Z table) at a precision of 5 % and CI of 95 %.

 = 0·84 (From Z table) at 80 % power.

d is effect size; estimated to be 9·4 μg/l for serum ferritin^(38)^ and 0·65 g/dl for Hb (anaemia)^(39)^.

Sample size (Serum ferritin): N = 2

(

*+*

*/*

= 72

Sample size (Hb): N = 2

(

*+*

*/*

= 53

The larger sample size (N = 72) of the 2 variables (serum ferritin and Hb) will be used for the study.

As a cluster randomised controlled trial, cluster design effect has to be considered in the sample size calculation to improve the power and precision of the study^(40,41)^. The required sample size for a cluster randomisation trial is obtained by multiplying the sample size of the individual randomisation trial (N = 72) by the design effect^(42,43)^. Design effect = 1 + intra-cluster correlation (m-1), where m is the average cluster size. An estimated intra-cluster correlation of 0·0009^(44)^ will be used. The average size of each cluster (school) in the study district is estimated to be 55 adolescent girls, with the number of anaemic adolescent girls in each school estimated to be 43^(32)^, thus m = 43. Design effect = 1 + 0·0009(43–1) = 1·037. Hence, considering the design effect of 1·037 and 15 % attrition rate, the sample size will be 86 participants per arm (258 participants for the 3 arms, with 43 participants to be chosen from each school).

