#### General characteristics

General characteristics of participants such as age, ethnicity, religion, level of education (class), educational and occupational statuses of their parents/guardians, household size, menarche status and age at menarche will be documented.

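### Menarche-related differences are to be explored by stratifying the analysis, with no arm-by-menarche interaction named; separate within-stratum tests do not test whether the effect differs

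*Protocol article*

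**What the plan says.** The article enrols girls before and after menarche together, on the ground that average iron requirement differs by only 0.3 mg between the two groups. It then adds that "data analysis will also be stratified by menarche status to explore any possible menarche status-related differences" (Study population). Under General characteristics, "menarche status and age at menarche will be documented", so the subgroup variable is collected at baseline.

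The Statistical analysis section compares the three arms on ferritin and Hb by one-way ANOVA with Tukey's post hoc test, looks at change within arms by paired t test, and relates covariates to outcomes by linear and logistic regression. P below 0.05 "will be considered significant at two-tailed tests". No arm-by-menarche term, or any other comparison of arm effects between the strata, is named.

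**The concern.** The stated aim is a difference between strata, and the only method given is to analyse the strata. Running the listed tests in each stratum answers two separate questions: is there an arm effect before menarche, and is there one after? Neither answers whether the two effects differ. The planned regressions, as described, concern how covariates relate to outcomes. That is a main effect of menarche status, not a change in the arm effect with menarche status.

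With two sets of P values and no direct comparison, a result that is significant in one stratum only is easily taken as evidence that the beverage works in one group and not the other. Each stratum holds only part of a sample sized for the whole arm, so that pattern is common even when the effects are equal.

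**Working it through.** **Inputs from the Sample size section**
- z for alpha: "1·96 (From Z table) at a precision of 5 % and CI of 95" %.
- z for power: "0·84 (From Z table) at 80 % power".
- Ferritin SD: "sd is standard deviation; estimated to be 20·1 μg/l for serum ferritin" (Hb 1.2 g/dl).
- Ferritin effect: "d is effect size; estimated to be 9·4 μg/l for serum ferritin" (Hb 0.65 g/dl).
- Design effect 1.037, attrition 15%, 86 girls per arm.

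**Input not in the documents:** the share of girls in each menarche stratum. It is assumed and varied (50:50, 30:70, 20:80).

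**Step 1, the plan's own figure.** n = 2 × (20.1 × 2.80 / 9.4)² = 71.7, so 72 per arm, as stated. 72 × 1.037 × 1.15 = 85.9, so 86, as stated. Hb gives 53.4 against the stated 53.

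**Step 2, power within a stratum (ferritin, 50:50).** Girls analysed per arm = 86 × 0.85 = 73.1; per stratum 73.1 / 2 = 36.55. SE of an arm difference = 20.1 × √(2/36.55) = 4.70. Effect / SE = 9.4 / 4.70 = 2.00. Power at two-sided 0.05 = Φ(2.00 − 1.96) = 0.516. With the Tukey cut-off for three arms (about 2.38), power = Φ(2.00 − 2.38) = 0.353.

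**Step 3, exactly one stratum significant when the true effect is the same in both.** P = p₁(1 − p₂) + p₂(1 − p₁), treating the strata as independent.
- 50:50, unadjusted: 2 × 0.516 × 0.484 = 0.50.
- 50:50, Tukey: 2 × 0.353 × 0.647 = 0.46.
- 30:70, unadjusted: powers 0.341 and 0.657, so 0.341 × 0.343 + 0.657 × 0.659 = 0.55 (0.50 with Tukey).
- 20:80, unadjusted: powers 0.244 and 0.715, giving 0.61 (0.55 with Tukey).
- Hb, unadjusted: 0.46, 0.54 and 0.63 at the three splits.
- All 86 per arm analysed, ferritin, 50:50, unadjusted: power 0.583, giving 0.49.

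**Step 4, dependence on the size of the common effect (ferritin, 50:50, unadjusted)**

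| Common effect, multiple of 9.4 µg/l | Power per stratum | Exactly one significant |
|---|---|---|
| 0 | 0.050 | 9.5% |
| 0.5 | 0.170 | 28% |
| 0.75 | 0.323 | 44% |
| 1 | 0.516 | 50% |
| 1.5 | 0.851 | 25% |

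**Step 5, the interaction test.** At two-sided 0.05 it signals a difference in 5% of trials with equal effects, whatever their common size or the split, provided its standard error is valid. At 50:50, SE of the difference between stratum effects = 20.1 × √(4/36.55) = 6.65. Power for a between-stratum difference of 9.4 µg/l: 9.4 / 6.65 = 1.41, giving about 29%. A difference of 2.80 × 6.65 = 18.6 µg/l is needed for 80% power.

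**The case against.** The strongest reply is that this argues from silence. The article does not say how a menarche-related difference will be judged, does not say that stratum P values will be compared, and does not rule out an interaction. A condensed article may leave the model for one exploratory analysis to a fuller plan that is not shown. No hypothesis and no primary or secondary outcome depends on it, and its wording already marks it as exploratory. This stands, and it limits the point to a suggested improvement. It does not remove the point, because the article names both an aim and a method, and that method alone does not meet the aim.

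Three stronger readings are tempting, and the documents do not support them.
- A reader might infer that about half of all trials with equal effects would show a false difference. That needs a common effect near 9.4 µg/l, a significant-versus-not rule the protocol does not state, and an assumed split. For a contrast with no true effect in either stratum, which could apply to the beverage against iron-folate if the two act alike, the rate is 9.5% unadjusted. With the Tukey cut-off it is only about 3% (2 × 0.017 × 0.983).
- A reader might take the RDA figures ("8 mg, 15 mg and 18 mg for girls aged" 10–13, 14–18 and 19 years) as evidence that the menarche groups should respond differently. Those figures are by age. The figure given for the menarche groups is the 0.3 mg difference.
- A reader might add that clustering makes the discordance worse. At the protocol's intra-cluster correlation of 0.0009 it is negligible. At an even split, power is already near one half, where 2p(1 − p) peaks, so losing power lowers the rate. School effects shared by both strata would also tend to make the stratum results agree.

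**Conclusion.** The point holds in a limited form. The protocol names stratification as the way to explore menarche-related differences and names no test or estimate of the difference between strata; separate within-stratum tests do not supply one. If the strata were nevertheless compared by significance, the pattern of one significant and one not would arise under equal effects in about 50% of trials at the planned ferritin effect and an even split (46% with Tukey), and in 25 to 28% at 1.5 times or half that effect.

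These figures rest on the protocol's planning values, 73 girls analysed per arm, an assumed menarche split, a normal approximation, independent strata and no clustering. The comparison of the arms in all girls is not affected. The point is minor: worth doing because it is easy, not because the trial's conclusions depend on it.

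**What to change.** Keep the planned stratum results, reported as arm differences with 95% CIs. Add one model for all girls with arm, baseline menarche status and their interaction, handling schools as in the main analysis. Report the interaction estimate with its 95% CI, and state that no conclusion will be drawn from comparing P values between strata. The exploratory status stays as it is.

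The cost is one extra model on data already to be collected: no additional girls, visits or measurements. The downside is low power, about 29% for a 9.4 µg/l difference between strata. The interval will therefore be wide, and the text should say in advance that a non-significant interaction is not evidence of equal effects.
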